### Secondary outcome measures

#### Performance measures

Physical performance measures will be assessed, which are less susceptible to bias due to patient unblinding. The four-square step test and sit-to-stand five times test will be used, as they have been validated in patients with pre-arthritic hip pain with effect sizes of − .63 and − .61, respectively [53]. These assessments will be completed at each site preoperatively, at 6 months, 12 months, and 24 months postoperatively. The score on these tests at each time point will be used for analysis. Mean scores between treatment groups will be compared at each time point.

#### PROMIS Global 10

General health-related quality of life will be measured using the PROMIS Global 10 assessment (Additional file 6). This 10-item tool assesses general domains of health-related quality of life in the domains of physical, mental, and social well-being [54]. Patients will complete this questionnaire pre-operatively and at the following time intervals post-operatively: 6, 12, and 24 months. The score at each time point will be used for analysis. Mean scores between treatment groups will be compared at each time point.

#### MRI T1ρ cartilage mapping

The association between hip arthroscopy outcomes and cartilage quality is not well elucidated in the literature. The quality of the hip articular cartilage will be assessed by a non-invasive and validated MRI technique called T1ρ mapping that enables the evaluation of proteoglycan content [55, 56]. The cartilage will be segmented on co-registered anatomical MR images and quantitative cartilage T1ρ values will be measured in six regions over the cartilage [57]. The T1ρ relaxation time is sensitive to the cartilage proteoglycan content and increasing when the proteoglycan content is decreasing. We will compare the cartilage T1ρ relaxation times at the initial scan and at the follow-up scan (24 months after surgery) in the different regions to investigate changes in the cartilage macromolecule content after surgery. The significance of the differences in T1ρ will be tested using a paired t-test with a significance level of *p* < 0.05.

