## Methods/design

### Principal research questions

The primary objective of this project is to assess the impact of concomitant hip arthroscopy with PAO for patients with symptomatic hip dysplasia on quality of life and cartilage health when compared to patients undergoing PAO only. The secondary objective is to investigate the cost utility of performing arthroscopy with a PAO from a healthcare utilization and societal perspective.

Our hypothesis is that concomitant hip arthroscopy at the time of PAO to address intraarticular pathology will result in significant improvements in quality of life and prevent further cartilage damage when compared to PAO alone. Also, we hypothesize that the additional costs associated with hip arthroscopy will be offset by greater clinical improvements and decreased cost consequences in this group and that combined hip arthroscopy and PAO will prove to be a cost-effective procedure.

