### Sample size and power calculation

A total sample size of 126 subjects is planned. Calculation of the required sample size is based on ensuring sufficient statistical power to detect a difference in the primary outcome measure (i.e., iHOT-33) at 12 months. The standard deviation of the iHOT-33 is approximately 16 in pre-arthritic patients [66–68]. The original iHOT-33 manuscript reported a minimal clinically important difference (MCID) of 6.1 in a general symptomatic hip population [66]. Since then, three other studies focusing on hip arthroscopy reported MCIDs varying from 10 to 12 [67–69] in time ranges varying from 6 to 12 months. Using a non-central *t* function with a conservative MCID of 10, an alpha level of 0.05, a power of 0.90, and a loss to follow-up of 15% provides a total sample size of 63 per group (total of 126).

For the T1ρ analysis, part of the subjects from each of the two subgroups will undergo quantitative hip cartilage MRI T1ρ-mapping. Our group has shown T1ρ to be a valid alternative to the gold standard (dGemric) for patients with symptomatic hip dysplasia (Additional file 1). Based on our hypothesis that patients undergoing in arthroscopy+PAO will conserve cartilage characteristics, whereas those with PAO only will demonstrate affected cartilage, the sample size for this study is calculated using a power analysis on T1ρ data from our longitudinal cartilage T1ρ study (two time points, mean follow-up time of 24.5 months) on corrective surgery for cam deformity in association with FAI [70]. Two years after surgery, T1ρ decreased significantly (*p* < 0.05) in the anterosuperior area of cartilage from 34.6 to 29.4 ms reaching control T1ρ values. By assuming a standard deviation of the mean T1ρ value of 5%, a power of 0.9, and alpha error of 0.05, we calculated that 21 subjects are needed for each of the two subgroups. Based on the follow-up loss rates from the former study (5 of 24; 20%) with this patient population, we will recruit a total of 26 patients per subgroup which will undergo the additional cartilage T1ρ-mapping protocol [57].

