### Analyses and frequency of analyses

The analysis will be conducted on an intention-to-treat basis. Statistical analyses will be performed blinded to treatment allocation. A level of significance of 0.05 will be used for all analyses. The underlying assumptions of all statistical procedures will be evaluated, and data transformation will be considered. Using descriptive statistics, baseline patient characteristic differences between the study groups will be assessed (age, sex, outcomes) and differences will be controlled for in the statistical analyses. Repeated measures mixed models and general linear mixed models will be used for handling continuous and dichotomous outcomes respectively. Sex will be specifically assessed as an effect modifier in the analyses. Multiple imputation will be considered as a sensitivity analysis.

For cartilage health, the biochemical content of the cartilage will be evaluated using MRI T1ρ mapping. The scan will be performed pre- and 2 years after surgery using a 3D turbo spin echo acquisition method with T1ρ preparation (CUBE QUANT) and the following parameters: TR = 1350 ms, TEeff = 40 ms, FOV = 25.6 × 25.6 cm^2^, in-plane resolution = 0.5 × 0.5 mm^2^, slice thickness = 3 mm, number of slices = 32 slices, no slice gap (3D sequence), B1 = 500 Hz, spin-lock times = 1, 15, 30, 45 ms, and scan time = 18 min [56, 71] (Additional file 1, Figure 3). For post-pressing, T1ρ-weighted datasets will be co-registered to the proton density-weighted turbo spin echo images and analyses described in our previous publications [57, 70]. The hip cartilage will be divided in six regions of interest (ROIs): anterior lateral, anterior middle, anterior medial, posterior lateral, posterior middle, and posterior lateral for regional proteoglycan assessment [57]. T1ρ values from the different cartilage regions will be compared and evaluated for significant differences between the pre-operative and the follow-up scan using repeated measures analysis of variance (ANOVA).

In addition to the final analysis, an interim analysis will be performed after 2.5 years to determine if the study must be terminated. This will be based on the following results: serious adverse events significantly higher in the experimental group, greater than expected beneficial effects, improbable statistically significant difference by the end of the study, and participant recruitment is severely lagging and unlikely to achieve the target.

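### The tests named for T1ρ compare scans before and after surgery; no between-arm T1ρ test is specified, although the cartilage hypothesis is between arms.

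*Protocol article*

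**What the plan says.** Under Principal research questions, the primary objective is the effect of concomitant arthroscopy "on quality of life and cartilage health when compared to patients undergoing PAO only". The hypothesis there is that it will "prevent further cartilage damage when compared to PAO alone". Two other sections take the same view. Sample size and power calculation sizes the imaging subgroup on the expectation that the combined arm keeps its cartilage while the PAO-only arm does not. Using the results of this trial presents T1ρ mapping as a comparison of arthroscopy with no arthroscopy.

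The T1ρ analysis is described in two places.

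- MRI T1ρ cartilage mapping (a secondary outcome): "We will compare the cartilage T1ρ relaxation times at the initial scan and at the follow-up scan (24 months after surgery) in the different regions", and then "The significance of the differences in T1ρ will be tested using a paired t-test", at the 0.05 level.
- Analyses and frequency of analyses: "T1ρ values from the different cartilage regions will be compared and evaluated for significant differences between the pre-operative and the follow-up scan", by repeated measures ANOVA.

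The second section also has a general sentence: "Repeated measures mixed models and general linear mixed models will be used for handling continuous and dichotomous outcomes respectively". Cartilage then gets its own paragraph and its own method.

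**The concern.** The hypothesis concerns a difference between randomized arms, but the contrast attached to T1ρ is the change between two scans of the same patient. A paired t-test has no term for arm. Run on all patients pooled, it says nothing about arthroscopy. Run separately in each arm, it gives two p-values and no estimate of the difference between arms.

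The only arm statement then available would be that one arm changed significantly and the other did not. That is not a valid test of a difference, and it gives up what randomization offers for this outcome. Cartilage health also stands in the primary objective while T1ρ is listed as a secondary outcome, so its weight in the conclusions is unclear.

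**Working it through.** **1. The passages side by side**

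| Measure | Contrast stated in the article |
|---|---|
| iHOT-33 | Group means at each time point, and proportions of patients improving by more than the MCID, compared between arms |
| Four-square step and sit-to-stand tests | Group means compared between arms at each time point |
| PROMIS Global 10 | Group means compared between arms at each time point |
| T1ρ, outcome section | Initial against 24-month scan, paired t-test |
| T1ρ, analysis section | Pre-operative against follow-up scan, repeated measures ANOVA |

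Of these measures, T1ρ is the only one without a stated arm comparison.

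**2. The plan's own figure: 21 per subgroup**

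Inputs from Sample size and power calculation: change 34.6 − 29.4 = 5.2 ms, SD 5%, power 0.9, alpha 0.05 (two-sided assumed).

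- SD as 5% of the mean: 0.05 × 34.6 = 1.73 ms, or 0.05 × 29.4 = 1.47 ms. An exact t calculation gives 4 per group, paired or two-sample. This does not reproduce 21.
- SD read as 5 ms (an assumption): d = 5.2/5 = 1.04. For a two-sample t-test the non-centrality is d√(n/2). With n = 21 this is 1.04 × √10.5 = 3.37 and power is 90.8%; with n = 20 power is 89.3%. This gives exactly 21.
- A paired t-test with SD of change 5 ms needs 12. With SD of change 5√2 ms (uncorrelated scans) it needs 22.

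On the 5 ms reading, 21 matches a two-arm comparison exactly. This suggests that an arm comparison was intended, but does not prove it.

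**3. What separate within-arm tests would do**

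Assumptions not in the article: the paired test is run in each arm, n = 21 per arm, SD of change 5 ms, and the same true change in both arms, so the true arm difference is zero. Let p be the power of one paired test, with non-centrality (change/5) × √21. The chance that exactly one arm is significant is 2p(1 − p).

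| True change, both arms | p | 2p(1 − p) |
|---|---|---|
| 0 ms | 0.050 | 9.5% |
| 1 ms | 0.141 | 24% |
| 2 ms | 0.415 | 49% |
| 3 ms | 0.744 | 38% |
| 4 ms | 0.936 | 12% |
| 5.2 ms | 0.995 | 1% |

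Example at 2 ms: 2 × 0.415 × 0.585 = 0.486. The formula cannot exceed 50%, so 2 ms is close to its worst case.

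**4. Whether the repaired analysis is workable with the planned scans**

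Take a between-arm difference of 5.2 ms, an SD of 5 ms at each scan and a pre-post correlation r (not in the article). ANCOVA has residual SD 5√(1 − r²); change scores have SD 5√(2(1 − r)).

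| r | ANCOVA: n per arm for 90% | ANCOVA: power at 21 | Change score: power at 21 |
|---|---|---|---|
| 0 | 21 | 91% | 64% |
| 0.3 | 19 | 93% | 79% |
| 0.5 | 16 | 97% | 91% |
| 0.7 | 11 | 99.6% | 99% |

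The 5.2 ms is a before-after change after cam surgery, not a between-arm difference. If the arms differ by half of it (2.6 ms), change-score power at 21 per arm is 21%, 29%, 38% and 57% at the same four correlations.

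**The case against.** The strongest reply is that the between-arm intent is plain in three sections and that the mixed-model sentence for continuous outcomes could cover T1ρ. An ANOVA with arm as a between-patient factor would also do. This stands in part. A reader might infer that the cartilage hypothesis will never be tested, and the documents do not support that. They show only that no between-arm T1ρ test is specified. The general sentence does not close the gap, because it names no T1ρ contrast and cartilage is then treated separately.

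Three further readings go too far.

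- **Two conflicting methods.** With two time points and no other factor, repeated measures ANOVA is the paired t-test (F = t²). The two differ in substance only if the ANOVA carries another factor, such as region or arm, and the text does not say whether it does.
- **A 49% false-claim rate.** The article does not say that tests will be run by arm, or that one significant arm will be taken as an effect. The figure holds at one assumed change; over the range shown it runs from 1% to 49%.
- **A powering region missing from the analysis.** The sample size refers to a change "in the anterosuperior area of cartilage from 34.6 to 29.4 ms reaching control T1ρ values", and that label is not among the listed regions. It comes from an earlier study of another condition, and whether it maps to one of the listed anterior regions cannot be settled from the article.

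Testing six regions at 0.05 gives 1 − 0.95⁶ = 26% only if the regions are independent, which is unlikely within one joint. Multiplicity control for a secondary imaging outcome is commonly left to the analysis plan.

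**Conclusion.** The point holds as a mismatch between question and test: the cartilage hypothesis is between arms, the tests named for T1ρ are before-after contrasts, and no between-arm T1ρ contrast is specified. This follows from the text and needs no assumed figure.

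The chance of a misleading one-arm-only result, about 1% to 49% for equal true changes of 0 to 5.2 ms, illustrates one possible reading. It rests on separate within-arm tests, 21 evaluable patients per arm and an assumed 5 ms SD of change.

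The effect is confined to the cartilage conclusions, which come from an imaging subgroup of 26 recruited per arm. The iHOT-33 comparison at 12 months is unaffected.

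**What to change.** - Bring the two T1ρ sections together on one between-arm analysis. One option is ANCOVA of 24-month T1ρ on arm and baseline T1ρ, adjusted for the stratification factors site and sex. Another is a mixed model with an arm-by-time contrast.
- Report the between-arm difference with a 95% confidence interval, and make within-arm change descriptive.
- Preferably name one main cartilage region in advance and treat the others as supportive.
- Make Principal research questions and the outcome sections agree on whether cartilage health is primary or secondary. Which it is remains the sponsor's choice.

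The cost is protocol wording: the same patients, scans and data serve. The change should be made before any T1ρ results by arm are seen.

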#### Adverse events

Adverse events will be systematically queried and documented prospectively for the first 90 days [58] using Sink et al.’s classification system that grades the complications based on required treatment and long-term morbidity [59] (Additional file 7). Any other unexpected adverse events that are reported by the study participants will also be recorded for the duration of the study. The type of adverse event will be narratively reported in any publications along with their severity using the classification of Sink et al. [58]. Reoperation rate will also be monitored at 12 and 24 months post-operatively in each group using standardized failure modes [60] (Additional file 7). Although a recent retrospective chart review has demonstrated that there were no differences in reoperation rates between PAO alone and PAO combined with arthroscopy at minimum 2-year follow-up [61], there are obvious limitations in regard to selection bias, a prospective randomized trial might show otherwise (see Figure 4 in Additional file 8 for the figure as per Spirit guidelines).

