Physical examination and radiographic follow-up assessments and measurements will be performed at regular intervals until the PAO has completely healed as part as standard of care. Radiographic control (well-centered AP pelvis and 45° Dunn view) done at the pre-operative time point, 2–4 weeks, 6 months, 12 months, and 24 months post-operatively, is the current standard of care at all institutions involved in the study [48]. Additional x-rays may be performed at the surgeon’s discretion. In addition to the standard of care treatment described above, patients will be randomized to either the *experimental group* or the *control group.*

Patients randomized to the *experimental group* will undergo central compartment hip arthroscopy prior to completion of the PAO. Diagnostic arthroscopy will first be performed, and intra-operative findings will be recorded on a standardized reporting form (Additional file 4). Hip arthroscopy will be carried out using the treating surgeon’s usual technique and will adhere to the following guidelines: a limited inter-portal capsulotomy may be made to allow sufficient space for visualization and instrumentation, if needed (a “T” capsulotomy should not be performed); labral refixation using a minimum of two suture anchors for any identified unstable labral tears; labral debridement should be reserved for only clearly irreparable tears or very small, stable tears; maximal preservation of any remaining intact labral tissue should be attempted; treatment of chondral lesions and ligamentum teres pathology may be performed at the surgeon’s discretion; and arthroscopic cam decompression should not be performed (Additional file 2). Patients randomized to the *control group* will undergo isolated PAO.

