### Proposed methods for protecting against sources of bias

The addition of hip arthroscopy represents a discrete intervention added on to the current standard of care for treatment of symptomatic hip dysplasia (i.e., PAO). Thus, a randomized trial represents the best study design for assessing its potential additive effect. Since the treating surgeon must administer the experimental intervention, a double-blind design is not possible.

Assessments that are not patient self-report and data analyses will be performed blinded to allocation. When submitting our feasibility protocol to our Research Ethics Board in the spring of 2018, we initially had indicated blinding of study participants through a diagnostic arthroscopy in the PAO-only patients (same incision as PAO+arthroscopy group). However, there were ethical implications with inserting a scope into the hip of the control group and therefore we converted the study design to a single-blinded methodology only, recognizing that this may introduce a potential source of bias in any patient-reported outcome measures. In addition to patient-reported outcomes, objective performance measurements, administered by blinded assessors, will be performed as one of the outcome measures. At each postoperative time point, patients will document through a standardized form conservative and surgical co-interventions targeting the treated hip and received after the previous time point.

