### Risks to safety of study participants

The risk of a PAO performed without hip arthroscopy may lead to untreated labral tears that may result in ongoing pain and require arthroscopy at a later time [60]. The risks of a PAO performed with a hip arthroscopy include the following: increased surgery time, fluid extravasation into the soft tissues resulting in increased hip/leg swelling, traction on the leg possibly increasing the risk of a nerve injury, partial capsulotomy which may lead to hip instability, and inadvertent damage to the labrum or cartilage as well as intra-articular adhesions. Although there are additional risks to performing an arthroscopy in addition to a PAO, it is hypothesized that arthroscopy will address intraarticular pathology, thereby minimizing cartilage damage and improving quality of life.

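### Adverse events are actively solicited only to day 90, so later foreseeable events that lead to no reoperation or recorded co-intervention have no stated systematic capture in either arm

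*Protocol article*

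**What the plan says.** The Adverse events section sets two successive rules. First, "Adverse events will be systematically queried and documented prospectively for the first 90 days", graded with a published classification of complications. Second, "Any other unexpected adverse events that are reported by the study participants will also be recorded for the duration of the study". It adds that "Reoperation rate will also be monitored at 12 and 24 months post-operatively in each group using standardized failure modes".

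Other parts of the article bear on late events:

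- Under Proposed methods for protecting against sources of bias, there is a form for every follow-up after surgery: "patients will document through a standardized form conservative and surgical co-interventions targeting the treated hip and received after the previous time point". The same section says that patients are not blinded, and accepts that this may bias what they report.
- Under Planned trial interventions, radiographs are "done at the pre-operative time point, 2–4 weeks, 6 months, 12 months, and 24 months post-operatively".
- Under Risks to safety of study participants, the risks of adding arthroscopy include "partial capsulotomy which may lead to hip instability, and inadvertent damage to the labrum or cartilage as well as intra-articular adhesions". Longer operating time, swelling from fluid leakage and a possible traction injury to a nerve are listed as well. The same paragraph gives PAO alone a risk of its own: labral tears left untreated, with continuing pain and possibly a later arthroscopy.
- Under Analyses and frequency of analyses, one ground for stopping at the interim is "serious adverse events significantly higher in the experimental group".

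**The concern.** After day 90 an event meets the recording rule only if it is both unexpected and volunteered. An event named in advance in the risk section is hard to call unexpected, and at that stage nobody is stated to ask about it. The events most worth comparing between arms, because the investigators foresaw them, are thus the ones the later rule does not call for.

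Reporting also moves from solicited to spontaneous, from patients who know which operation they had. Willingness to mention a problem may differ by arm. What is at stake is whether the trial can give a complete, even-handed account of harms over its 24 months, to set beside the quality-of-life and cost results.

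**Working it through.** The article gives no figure for adverse-event capture, so there is none to reproduce. The check is to follow a late event through each stated route of capture.

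**Step 1. Time covered by active querying.** Inputs: a 90-day window (Adverse events), the primary time point at 12 months and last follow-up at 24 months (Primary outcome measure).

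- Share of 24 months: 90 / 730.5 = 12.3%.
- Share of the 12 months to the primary time point: 90 / 365.25 = 24.6%.
- Remainder of the 24 months: 100% − 12.3% = 87.7%.

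These are shares of calendar time only.

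**Step 2. What each route records after day 90.**

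| Route (section) | Records | Does not record |
|---|---|---|
| Participant reports (Adverse events) | Unexpected events that are volunteered | Foreseen events; anything not volunteered |
| Reoperation monitoring at 12 and 24 months (Adverse events) | Events that lead to further surgery, by group | Events managed without surgery |
| Co-intervention form at each postoperative time point (Proposed methods for protecting against sources of bias) | Conservative and surgical treatment of the treated hip | Events without treatment; no event diagnosis or grade is stated |
| Radiographs at 6, 12 and 24 months (Planned trial interventions) | Standard-of-care imaging | No stated link to adverse-event recording |
| T1ρ MRI at 24 months (MRI T1ρ cartilage mapping; Sample size and power calculation) | Cartilage proteoglycan content in 26 + 26 = 52 of 126 patients (41%) | The other 74 patients; clinical events |

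**Step 3. What passes through every route.** Take adhesions or instability that become apparent at nine months and are only observed. They are foreseen, so the participant-report rule does not call for them. They lead to no surgery and no treatment, so neither the reoperation record nor the form shows them. The same holds for continuing pain from an untreated labral tear in a PAO-alone patient who has no further treatment. The gap is therefore late, foreseen and untreated events, in both arms.

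**Step 4. Visits available to close it.** The iHOT-33, the performance tests and the PROMIS Global 10 are already collected at 6, 12 and 24 months in all patients. The article states no adverse-event query at these visits.

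**The case against.** The strongest reply is that late capture is better than the 90-day sentence suggests. Reoperations are followed by group with standardized failure modes, and the co-intervention form covers conservative as well as surgical treatment in both arms. The grading system rests partly on the treatment required, so treatment records carry much of what is needed to grade an event. This stands: most treated late events should be traceable, and it confines the gap to the untreated ones.

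A second reply is that the adverse-event and failure-mode forms are in an additional file that is not shown and may hold more detail. That is possible, so the finding is that no later query is stated. But the 90-day limit and the restriction to unexpected events are rules written in the article itself, not details left to a form.

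Three stronger readings are tempting and not supported:

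- A reader might infer that the protocol itself lists these harms as late. Its risk section gives no timing for any arthroscopy harm. Fluid extravasation and traction injury are perioperative by nature and fall inside the 90 days. That instability or adhesions may show later is a reasonable inference, not a statement in the document.
- A reader might infer bias toward no difference, favouring arthroscopy. The gap applies to both arms, PAO alone has its own listed later problem, and spontaneous reporting by unblinded patients could move the comparison either way.
- A reader might infer that the interim safety criterion is compromised, or that 88% of harms go unseen. The criterion concerns serious events, and untreated events are the least likely to be serious. Reoperations are tracked, and the data safety monitoring board compares safety by group one year after recruitment starts and every six months thereafter. Nothing suggests that harms are spread evenly over follow-up.

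**Conclusion.** The point holds in a limited form. As written, the protocol solicits adverse events only to day 90 and afterwards calls only for unexpected, volunteered ones. Foreseeable events in either arm that present later, without reoperation or recorded co-intervention, have no stated systematic capture or grading. The between-group harm comparison to 24 months is incomplete, with possible differential reporting of unknown direction.

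The number of events affected cannot be estimated, because the article gives no rates or timing. The conclusion assumes that some foreseen events can first appear after 90 days, and that the forms not shown do not add a later query. The primary outcome and its sample size are untouched. This is an inexpensive improvement to the harm data, not a flaw that threatens the trial's main result.

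**What to change.** Three changes to data collection and reporting, with no change to patient care:

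1. Repeat the same standardized adverse-event query and grading at the existing 6-, 12- and 24-month visits, identically in both arms, asking about the period since the last query.
2. Delete the word *unexpected* from the rule for events after day 90, so that any reported event is recorded.
3. Report events to day 90 and events to 24 months separately by arm, so that the 90-day results stay comparable with the window already chosen.

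The cost is one existing form used at three existing visits: a few minutes of coordinator time each, and somewhat more events to grade. Because patients may reveal their allocation when answering, the query is best put by someone other than the blinded performance assessor.

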### Anticipated compliance problems

We do not anticipate compliance problems, as the interventions are one-time surgeries. If patients cross over from one treatment group to another after randomization, their results will still be included in the final analysis on an intention-to-treat basis. All attempts should be made to avoid patient cross-over and if cross-overs do occur after randomization, the reason for this will be recorded. The aim of the pilot was to test the methods and optimize data collection procedures. If that data is shown to be applicable to the current proposal, it will be included.

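### Adverse events are to be published as a narrative of type and severity, with no between-arm estimate or interval for complications of the added arthroscopy

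*Protocol article*

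**What the plan says.** All references are to the protocol article.

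- **Collection** (Adverse events): "Adverse events will be systematically queried and documented prospectively for the first 90 days", graded with a published classification based on treatment required and long-term morbidity. Other unexpected events that participants report are recorded for the whole study.
- **Publication** (same section): "The type of adverse event will be narratively reported in any publications along with their severity".
- **Reoperation** (same section): "Reoperation rate will also be monitored at 12 and 24 months post-operatively in each group using standardized failure modes".
- **Monitoring**: Analyses and frequency of analyses lists significantly more serious adverse events in the experimental group among the grounds for termination at interim. The section on the steering committee and the data safety monitoring board (DSMB) has the DSMB compare adverse event variables by intervention group.
- **Risks**: Risks to safety of study participants begins its closing sentence "Although there are additional risks to performing an arthroscopy in addition to a PAO". It has just listed fluid extravasation, a possible increase in nerve injury from traction, instability after capsulotomy, inadvertent labral or cartilage damage, and adhesions.
- **Analysis basis**: "The analysis will be conducted on an intention-to-treat basis". For patients who cross over, Anticipated compliance problems says "their results will still be included in the final analysis on an intention-to-treat basis" and has the reason recorded.

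**The concern.** The trial asks whether a discrete procedure is worth adding to a periacetabular osteotomy (PAO). For the iHOT-33, the performance tests and the PROMIS score, the article says that group means will be compared at each time point. Costs and quality-adjusted life years get 95% intervals. For complications, the stated published output is a description of types and grades.

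A reader would then have a benefit estimate with its uncertainty beside a harm account without any. Two short lists of complications look alike unless the difference is large, and a narrative does not show how large an excess remains compatible with the data. The event types do not settle the matter either. The protocol describes traction as possibly increasing the risk of nerve injury, and it allows an anterior arthrotomy in either arm when motion is limited after the PAO. Some events may therefore occur in both arms, and it takes a comparison of frequencies to show an excess.

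**Working it through.** **Plan's own figure.** Sample size and power calculation gives SD 16, difference 10, alpha 0.05 (two-sided assumed), power 0.90 and 15% loss. The normal approximation gives 2 × (1.960 + 1.282)² × 16² / 10² = 53.8, so 54 per group. Allowing for loss gives 54 / 0.85 = 63.5 (64) or 54 × 1.15 = 62.1 (63). The non-central t gives 55, then 65 or 64. The stated 63 per group is within two patients of every variant and is used below. It was set for the iHOT-33, not for harm.

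**Assumptions.** The document gives no adverse event rate and no cross-over rate. All such rates below are assumed.

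**Equal rates of 10%.** Half-width = 1.96 × √(2 × 0.10 × 0.90 / 63) = 0.105. Identical observed rates would still be compatible with an excess of about 10.5 points in the arthroscopy arm, roughly a doubling (10% to 20.5%).

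**No events of one type.** For 0 of 63, the one-sided 95% upper limit is 1 − 0.05^(1/63) = 4.6%.

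**Other rates, 63 per arm.** Half-width = 1.96 × √[p₀(1 − p₀)/63 + p₁(1 − p₁)/63]; power is at two-sided 0.05.

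| PAO alone | With arthroscopy | 95% half-width (points) | Power |
|---|---|---|---|
| 5% | 10% | 9.2 | 18% |
| 5% | 15% | 10.3 | 46% |
| 5% | 20% | 11.2 | 73% |
| 10% | 20% | 12.3 | 35% |
| 10% | 25% | 13.0 | 60% |

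A doubling from 5% or from 10% would usually miss significance even with all 63 per arm. Failure to meet the interim harm criterion would therefore say little about whether an excess exists.

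**Cross-over.** If a share c₀ of the PAO arm receives arthroscopy and a share c₁ of the arthroscopy arm does not, the assigned-arm difference is the true difference × (1 − c₀ − c₁). For an assumed 10-point excess:

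- 5% each way: 10 × 0.90 = 9.0 points.
- 10% each way: 10 × 0.80 = 8.0 points.
- 5% or 10% of the PAO arm only: 9.5 or 9.0 points. The excess events counted under PAO alone are 63 × 0.05 × 0.10 = 0.3 or 63 × 0.10 × 0.10 = 0.6.

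These shifts of 0.5 to 2 points are small beside half-widths of 9 to 13 points.

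**The case against.** The strongest reply is that the sentence does not say that events will be reported only narratively. Reoperation is monitored in each group, serious adverse events are contrasted at interim, the DSMB compares adverse events by group, and a model for dichotomous outcomes is named. A reader might infer that the trial never estimates the added risk of arthroscopy, and the documents do not support that. Comparison by assigned arm is the randomised contrast and does estimate added risk, diluted by any cross-over.

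A reader might also infer that intention to treat is an error here because it books arthroscopy complications to PAO alone. That does not follow. The sentence on cross-overs speaks of results and does not mention adverse event attribution. No cross-over rate is given, cross-over is to be avoided, and "We do not anticipate compliance problems, as the interventions are one-time surgeries". At the assumed rates the dilution is small.

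Finally, safety sets and harm tables are commonly left to a statistical analysis plan or full protocol, neither of which is shown. That stands for a table by procedure received, whose absence is not a fault. It does not fully answer the publication sentence, which is a positive statement covering any publications. The interim and DSMB comparisons serve monitoring, and nothing in the article says that they will yield a published estimate.

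**Conclusion.** The point holds as one about the stated output. The article fixes a narrative of type and severity as the published form for adverse events and states no between-arm estimate or interval for complications, although its own stopping criterion and DSMB remit need such a contrast. At 63 per arm the unstated uncertainty is about 10.5 percentage points either way for an assumed 10% rate in both arms, and about 9 to 13 points over assumed rates of 5% to 25%. No stated figure is wrong, and the primary analysis is unaffected. The cross-over aspect is conditional on rates that the document does not give and calls for no change to intention to treat.

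**What to change.** In the Adverse events section, replace the publication sentence with a commitment to report the number and percentage of patients with at least one event, by assigned arm and by grade. Give a risk difference with 95% interval for any complication, for higher-grade complications (the grade cut-off fixed in advance) and for reoperation at 12 and 24 months. Keep narratives for individual serious cases.

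If cross-overs occur, a second table by procedure actually received at the index surgery may be added, labelled supportive and not protected by randomisation.

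The cost is a change of wording and one or two tables. Events are already queried prospectively and graded, and reasons for cross-over are already recorded. The intervals will be wide: the change shows how imprecise the harm data are and does not make them more precise.
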